##### Exploratory outcomes

HbA1c at 18 months after delivery of intervention may be collected from the ANDA 2023 audit.

### Participant timeline {13}

The participant timeline is presented in Fig. 2.

**Fig. 2 Fig2:**
[figure not shown]
ANDA-EFFECT SPIRIT figure [22]

### Sample size {14}

Sample size calculation is based on a cluster randomised trial design with the difference in HbA1c as the primary endpoint. Assuming a mean difference in the intervention group of 0.5%, a total sample size of 3500 patients, 35 sites in each arm will provide at least 80% power assuming that the standard deviation of HbA1c is 2.3, the intracluster correlation coefficient is 0.070 and the coefficient of variation of cluster sizes is 0.730. We thus plan to recruit 78 diabetes centres: 39 in each arm to allow for a 10% non-response rate. Sample size calculation was based on the difference in means calculation with the level of significance set at 0.05. PASS V14 software [23] was used for the sample size calculation.

## Assignment of interventions: allocation

### Sequence generation {16a} and implementation {16c}

The random allocation sequence was generated by a senior biostatistician independent to the study in order to allocate the participating diabetes centres (clusters) into the experimental group (enhanced feedback and cointervention) and the control group (enhanced feedback) using random block sizes 2 and 4, stratified by type of centre (primary/secondary care vs tertiary care or Centres of Excellence (CoE)) and location (metropolitan or rural), based on centres who participated in ANDA 2019. Due to the low numbers of Centres of Excellences and the similarity to tertiary care centres, these types of centres will be combined for the purpose of stratification and analysis. We based the randomisation on 2019 ANDA participation and randomised prior to the formative qualitative work [16] to avoid potential contamination of the trial control group. As such, randomisation occurred prior to commencement. In addition, any centres who participated in ANDA for the first time in 2021 were allocated to either the intervention or the control arm as per the outlined randomisation method. Participants will be enrolled by the project lead as per section {26a}.

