**Methods:**

Two-armed cluster randomised trial with Australian Diabetes Centres that participated in the Australian National Diabetes Audit in 2021 as the clusters, stratified by location and type of centre. We aim to recruit 35 diabetes centres in each arm. Both the intervention and control arms will receive an augmented feedback report, accompanied by a partially pre-populated slide deck. In addition, the intervention arm will receive a tailored theory-based intervention designed to address identified, modifiable barriers to utilising and implementing the recommendations from diabetes audit feedback. The co-primary outcomes are (1) HbA1c at the patient level, measured at 6 months after delivery of the intervention, and (2) the acceptability and utility of the augmented feedback and cointerventions at the practitioner level, measured at 3 months after delivery of the intervention.

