## Statistical methods

### Statistical methods for primary and secondary outcomes {20a}

#### Primary outcomes

Differences between the experimental and control groups will be analysed by the intention-to-treat approach. For the first co-primary outcome of difference in HbA1c, we will use the linear mixed effects model to compare the between-group difference in mean HbA1c at 6 months after delivery of the intervention while adjusting for clustering of patients with site by including a centre random intercept. Appropriate transformations of the data will be undertaken in the event of departure from normality. Only if the first co-primary outcome is statistically significant at a two-sided level of significance of <0.05, we will test the second co-primary of acceptability and utility of interventions for superiority using the chi-squared or Fisher’s exact test as appropriate. This will preserve the overall type 1 error at <0.05.

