#### Secondary outcomes

Other secondary clinical endpoints (e.g. mean LDL-Ch) and exploratory outcomes (e.g. mean HbA1c at 18 months) will similarly be analysed using the linear mixed effects model.

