### Methods for additional analyses (e.g. subgroup analyses) {20b}

Additional subgroup analyses are not planned in this trial.

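### Centre type and location stratify the randomisation, but the models for HbA1c and the secondary outcomes name neither, although the protocol says the grouped centre type serves the analysis

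*Protocol article*

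**What the plan says.** The abstract describes the trial as "stratified by location and type of centre". The section on sequence generation {16a} gives two levels for each factor: primary or secondary care against tertiary care or Centre of Excellence, and metropolitan against rural. That makes four strata, filled with random blocks of 2 and 4. On the grouping of centre types it adds that "these types of centres will be combined for the purpose of stratification and analysis".

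The statistical methods {20a} describe the HbA1c analysis as a linear mixed effects model comparing the arms at 6 months, "adjusting for clustering of patients with site by including a centre random intercept". No other term is named. Other clinical endpoints "will similarly be analysed using the linear mixed effects model". The survey co-primary is tested by chi-squared or Fisher's exact test. Item {20b} states: "Additional subgroup analyses are not planned in this trial". So no described analysis uses centre type or location.

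On timing, item {16a} says: "We based the randomisation on 2019 ANDA participation and randomised prior to the formative qualitative work". Eligibility {10} then requires participation in the 2021 audit and written consent.

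**The concern.** The sequence-generation section gives grouped centre type a role in the analysis; the statistical methods give it none. An analyst working from the first would put centre type in the model, and one working from the second would not.

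Stratified allocation makes the arms alike on the two factors, so the effect estimate varies less from one randomisation to another. A model without the factors counts the differences between strata as random centre variation and reports a standard error that ignores this gain. Confidence intervals are then wider than they need be and the test rejects too rarely. Power matters more than usual here. The section on adherence strategies {11c} concedes that optimal sample size may be hard to reach, and the survey co-primary is tested only if HbA1c is significant.

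**Working it through.** **Inputs from Sample size {14}:** difference 0.5, SD 2.3, intracluster correlation 0.070, coefficient of variation of cluster size (CV) 0.730, k = 35 centres per arm, 3500 patients (m = 50 per centre), alpha 0.05, taken as two-sided from {20a}.

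**Assumed input:** the share R of between-centre HbA1c variance explained by the strata. The documents give no figure, so 0% to 40% is shown.

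**Step 1, the plan's own figure.** Between-centre variance is 0.070 × 2.3² = 0.370; within-centre variance is 0.930 × 2.3² = 4.920.

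- L = m × 0.070 / (m × 0.070 + 0.930) = 3.5 / 4.43 = 0.790.
- Relative efficiency with unequal clusters: 1 − CV² × L(1 − L) = 0.912.
- Design effect: 4.43 / 0.912 = 4.86.
- SE = √(2 × 5.29 × 4.86 / 1750) = 0.171.
- Power = Φ(0.5 / 0.1714 − 1.96) = 83.1%, or 82.0% with t on 68 degrees of freedom.

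This agrees with the stated 80% or more. The cruder design effect 1 + ((CV² + 1)m − 1) × 0.070 = 6.30 gives 72.7%, which does not, so the first form is used.

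**Step 2, with strata in the model.** Replace 0.370 by b = 0.370 × (1 − R) and recompute:

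SE_adj = √[2(b + 4.920/50) / (35 × RE)], where RE = 1 − CV² × L(1 − L) and L = 50b / (50b + 4.920).

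At R = 20%: b = 0.296, L = 0.751, RE = 0.900, SE_adj = 0.158.

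**Step 3, with strata left out.** The model still reports 0.171. Under balanced strata the true SD of the estimate is close to SE_adj. Hence:

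- Excess = 0.1714 / SE_adj − 1.
- Type I error = 2[1 − Φ(1.96 × 0.1714 / SE_adj)].
- Unadjusted power = Φ((0.5 − 1.96 × 0.1714) / SE_adj).
- Adjusted power = Φ(0.5 / SE_adj − 1.96).

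| R | SE_adj | Reported SE too large by | Type I error, unadjusted | Power, unadjusted | Power, adjusted | Points lost |
|---|---|---|---|---|---|---|
| 0% | 0.171 | 0% | 0.050 | 83.1% | 83.1% | 0 |
| 10% | 0.165 | 4% | 0.042 | 84.0% | 85.8% | 1.8 |
| 20% | 0.158 | 8% | 0.034 | 85.0% | 88.5% | 3.5 |
| 30% | 0.151 | 13% | 0.026 | 86.1% | 91.1% | 5.0 |
| 40% | 0.144 | 19% | 0.019 | 87.3% | 93.6% | 6.2 |

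**Step 4, simulation check.** 70 centres in four strata, blocks of 2 and 4, were fitted with and without stratum terms. At R = 0% the mean reported SE was 0.172 against a true SD of 0.171, with rejection rates under no effect of 0.044 and 0.043. At R = 20% without strata, it was 0.172 against 0.162, type I error 0.037, and power 84.0% against 87.7% adjusted.

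**Step 5, attrition from the list.** Suppose only half of the randomised centres take part (assumed, and unrelated to arm). At R = 20% the unadjusted reported SE is 0.173 against a true SD of 0.168, an excess of about 3%, with type I error 0.039. Adjustment brings the true SD to 0.162. With full participation that step was only from 0.162 to 0.160. So the SE excess shrinks, but adjustment does more for the estimate itself.

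**The case against.** The strongest objection is that the article is condensed. It names the model class, the contrast and the handling of clustering, and never says that nothing else enters. An analysis plan that is not shown may list both factors, and the remark that the grouping serves the analysis suggests as much. This stands as a limit: the protocol cannot be said to exclude the factors. It does not remove the mismatch, because one section gives centre type a use and the section that describes the model gives it none.

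Four stronger readings are tempting and are not supported.

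- *The standard errors are too wide as a matter of fact.* This holds only as far as the strata predict HbA1c, and the documents give no figure for that.
- *The benefit of stratifying is thrown away.* It is not. At R = 20% the unadjusted estimate has a true SD of 0.162 against 0.160 adjusted. What is lost is credit for it in the reported SE and the test. For the same reason, adjusted power must be compared with unadjusted power at the same R. Comparing it with the 0% baseline turns 3.5 points at 20% into 5.4 (88.5 − 83.1).
- *Omission biases the estimate because centres dropped out after randomisation.* The blinding section {17a} keeps centres unaware of their arm until the interventions are delivered, so consent should not depend on arm. Any imbalance from this source is chance, not bias.
- *The survey analysis needs the same terms.* Chi-squared and Fisher's exact tests take no covariates, so this would mean replacing the test, which is a separate matter.

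**Conclusion.** The point holds as an internal mismatch with a conservative consequence. If the HbA1c model is fitted as described and the strata explain 10% to 40% of between-centre variance, the reported SE is about 4% to 19% too large, type I error is about 0.042 to 0.019, and about 2 to 6 points of power are lost. These sizes rest on the assumed share, on the sample-size inputs and on balanced strata. They shrink towards zero as the share does, and the SE excess also shrinks as centres on the 2019 list drop out. No conclusion of the trial would be invalidated, and the stated power is reached without adjustment (82.0% to 83.1%). It is worth correcting because the gain is nearly free and the analysis would then match the way the centres are randomised.

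**What to change.** In the statistical methods {20a}, state that the linear mixed models for HbA1c and for the continuous secondary outcomes include centre type (primary/secondary against tertiary/Centre of Excellence) and location (metropolitan against rural) as fixed effects, with the centre random intercept kept. This brings the model into line with the sequence-generation section. If the omission is deliberate, say so and remove the reference to analysis from that section. The survey test is outside this change.

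The cost is one sentence and two of about 68 degrees of freedom. No new data are needed: the concealment section {16b} says the independent statistician's file held the stratification variables, and centres new in 2021 were allocated by the same method.

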### Concealment mechanism {16b}

The independent statistician was provided with a file containing only the diabetes centre identification codes and stratification variables and no identifying information.

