## Assignment of interventions: blinding

### Who will be blinded {17a}

The project lead and primary investigator will not be blinded to group allocation as they will be delivering the interventions, but they will only be aware of the site practice and outcome data pertaining to any given diabetes centre in a coded manner, as each participating diabetes centre has a unique identifying code. The ANDA Secretariat is the only person who has access to the codes linking diabetes centre IDs with their contact details and is not involved in the delivery of the intervention, assessment of outcome or analysis.

Other investigators and the biostatistician supervising the analysis will be blinded to group allocation. The data analysis team will be blinded to allocation details for the purpose of data analysis.

Participating diabetes centres will be blind to group allocation until the delivery of the interventions. Due to the nature of the intervention and control in this study, it will not be possible to blind the participating sites to the intervention they receive.

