### Data management {19} and confidentiality {27}

All data will be downloaded and electronically stored in line with applicable privacy principles. As part of ANDA data management, data collected with the standardised data collection form is checked by the data management team, with queries sent to participating diabetes centres regarding any data anomalies (such as out-of-range data). Once the data queries have been resolved, the ANDA dataset is checked by an independent data specialist [13].

All data will be password protected and will be housed on a secure Monash University Server, as per standard ANDA protocol [8]. The chief investigator, data manager and project lead will be the only researchers to have access to the data. All researchers on this project are involved in projects using research databases which have high levels of security. This electronic database will remain in password-secured storage for 7 years and then deleted from all backups.

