## Trial status

Protocol version: 2.0. Recruitment commenced for this trial on August 9, 2021. We anticipate a 6-week recruitment period.

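### Centres were randomised before consent and are enrolled by an unblinded project lead, and the stated concealment does not hide allocation from that role

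*Protocol article*

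**What the plan says.** All references are to the protocol article.

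- **Order of events.** Sequence generation {16a} and implementation {16c}: "We based the randomisation on 2019 ANDA participation and randomised prior to the formative qualitative work", and "As such, randomisation occurred prior to commencement". Trial status: "Recruitment commenced for this trial on August 9, 2021", with a 6-week window. Eligibility criteria {10} requires both written consent and participation in the 2021 audit.
- **Who enrols.** Section {16a}/{16c}: "Participants will be enrolled by the project lead as per section {26a}". Under Who will take informed consent? {26a}, centres tell the project lead that they wish to take part. The signed form goes to the Secretariat or to the project lead, and the project lead countersigns. The sender of reminders is not named.
- **What that role knows.** Who will be blinded {17a}: "The project lead and primary investigator will not be blinded to group allocation as they will be delivering the interventions".
- **Concealment.** Concealment mechanism {16b} consists of one sentence: "The independent statistician was provided with a file containing only the diabetes centre identification codes and stratification variables", with nothing that identifies centres.
- **Data access.** Section {17a} promises that the supervising biostatistician and the analysis team are blinded. Data management {19} and confidentiality {27} says: "The chief investigator, data manager and project lead will be the only researchers to have access to the data". Data Availability gives the final dataset to the project lead and the primary investigator.

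**The concern.** Allocation concealment means that whoever decides, or influences, which units enter the trial cannot know their arm. Here the arm of every centre on the 2019 list was fixed before anyone was asked to consent, and the role that takes consent is one the protocol declares unblinded. If that role knew the arms during recruitment, effort in explaining, reminding and following up could differ between arms, even without intent. The consenting centres in the two arms could then differ for reasons other than chance. An analysis by assigned arm would not correct this, because the selection happens before the analysis set is formed.

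The blinding of the analysis is a separate matter. If the blinded team is not among those with access to the data while an unblinded role is, the promised safeguard cannot operate as written.

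**Working it through.** The point is one of design, so the check sets the sections side by side.

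**1. Allocation came before consent.** Sections {16a}/{16c} put randomisation before the qualitative work and before commencement. Trial status puts the start of recruitment at 9 August 2021. For centres on the 2019 list the order is therefore certain. Centres new in 2021 were allocated by the same method, but the timing relative to their consent is not given.

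**2. The concealment text does not cover the enroller.** Section {16b} describes what the statistician could not see, namely which centre was which. That protects the generation of the sequence. It says nothing about what the project lead could see while recruiting.

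**3. When the project lead can link arm to name is not stated.** Two statements bear on this.
- Section {26a} says that the project lead knows the names of participating staff but not their centre's audit code. Section {17a} says that only the Secretariat holds the link between codes and contact details. A purely coded list would therefore not reveal the arm of a named centre.
- Section {17a} also has the project lead deliver the interventions and keeps the Secretariat out of delivery. The intervention components section has the project lead moderate the forums. By delivery, then, arm and name must be joined for that role.

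The dates leave little room between the two. The window closes at 9 August + 42 days = 20 September 2021. The resources open about 3 months before the December 2021 report, which is about September 2021. The arms may have become known just after recruitment closed, or before. The protocol does not say.

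**4. The analysed set.** Section {20c} defines intention to treat as keeping non-adherent sites in their assigned arm. Section {18b} keeps clinical outcome data from sites that withdraw. Neither brings in randomised centres that did not consent. The set compared is therefore the consenting, eligible subset of those randomised. This follows from {10} read with {16a}; the protocol does not state it outright.

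**5. What the sample size section adds.** 35 / 0.90 = 38.9, rounded up to 39 per arm, or 78 centres, as the protocol states. This 10% is an allowance for reaching the target number. It does not show how many centres were randomised or which of them consented. The number randomised is not given, so the share lost between randomisation and consent cannot be calculated.

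**6. Data access.** Section {17a} has a blinded biostatistician and a blinded analysis team. Section {19}/{27} admits only three researcher roles, and the biostatistician is not among them while the unblinded project lead is. Data Availability names the project lead and the primary investigator, the two roles that {17a} calls unblinded. The three statements cannot all hold as worded.

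**The case against.** The case on the other side is substantial. Under Recruitment {15} the Secretariat sends the invitations. Section {17a} keeps centres blind until delivery, so a centre decides without knowing its arm, and arm-dependent consent would need arm-dependent persuasion. No section reports any. The unblinding in {17a} is tied to delivery, and the coding in {26a} may have kept arms from the project lead during recruitment. All of this stands, and it lowers the risk. It does not close the route, because consent contact and countersignature remain with the project lead and no section says that the arms were withheld until then.

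A reader might infer more than the documents support:

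- **That concealment was broken.** It is undescribed for the enroller; nothing shows that it failed.
- **That arm was used to choose centres for the formative study.** Centres were "randomised prior to the formative qualitative work [16] to avoid potential contamination of the trial control group". This suggests such use but does not state it, and that study is not at hand.
- **That the project lead opens password access by arm.** The protocol says only that resources are password-protected and that the research team makes them available.
- **That centres missing the 2021 audit bias the comparison.** The eligibility rule is the same in both arms. Audit collection runs in May to July, before recruitment opened, and nothing links participation to arm. Such losses cost precision but do not by themselves bias.
- **That the bias can be sized.** The planning values give a between-centre SD of sqrt(0.070) × 2.3 = 0.61 HbA1c points. Any shift in those units due to selective consent would be an arbitrary choice.
- **That data access itself weakens concealment.** Section {17a} says that the two unblinded roles see outcome data in coded form. Access bears on the blinding of the analysis, not on enrolment.

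**Conclusion.** The point holds in limited form. Centres on the 2019 list were randomised before consent. The enrolling role is unblinded by the protocol's own statement, and the stated mechanism does not conceal allocation from it. The safeguards reduce the risk of arm-dependent recruitment without removing it. The analysed centres are a consenting subset of those randomised, so their number and balance by arm need to be shown.

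The size of any bias cannot be estimated. That would need the numbers randomised, eligible and consenting by arm, and the relation between consent and centre HbA1c. The documents give none of these.

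The conclusion assumes that the full protocol contains no fuller description of who held the allocation list and until when. The inconsistency over data access stands independently of the enrolment point.

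**What to change.** **Enrolment.** Have the Secretariat, which already sends invitations and keeps the enrolment records, handle all invitations, reminders and consent forms. Withhold the allocation list from the project lead until the 6-week window closes. The Secretariat does not need the list for this work either, and since it holds the link between codes and contacts, giving it the list would only move the problem. If recruitment has already finished, state the date on which the project lead learned the arms of named centres.

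**Reporting.** Give the numbers of centres randomised, eligible and consenting in each arm.

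**Analysis blinding.** Reconcile {17a} with {19}/{27} and Data Availability. Name the blinded biostatistician and analysis team as having access to a dataset with masked arm labels. Keep arm-linked outcomes from the project lead and primary investigator until the primary analysis is locked.

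**Cost.** A small shift of administrative work to the Secretariat, a short set of counts by arm and a few corrected sentences. By the dates above, no delay is expected, because the window closes at about the time the resources open.
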